## Abstract

**Background:** Tuberculous meningitis (TBM) is the most lethal form of tuberculosis with a mortality of ~50% in those co-infected with HIV-1. Current antibiotic regimens are based on those known to be effective in pulmonary TB and do not account for the differing ability of the drugs to penetrate the central nervous system (CNS). The host immune response drives pathology in TBM, yet effective host-directed therapies are scarce. There is sufficient data to suggest that higher doses of rifampicin (RIF), additional linezolid (LZD) and adjunctive aspirin (ASA) will be beneficial in TBM yet rigorous investigation of the safety of these interventions in the context of HIV associated TBM is required. We hypothesise that increased dose RIF, LZD and ASA used in combination and in addition to standard of care for the first 56 days of treatment with be safe and tolerated in HIV-1 infected people with TBM.

**Methods:** In an open-label randomised parallel study, up to 100 participants will receive either; i) standard of care (n=40, control arm), ii) standard of care plus increased dose RIF (35mg/kg) and LZD (1200mg OD for 28 days, 600mg OD for 28 days) (n=30, experimental arm 1), or iii) as per experimental arm 1 plus additional ASA 1000mg OD (n=30, experimental arm 2). After 56 days participants will continue standard treatment as per national guidelines. The primary endpoint is death and the occurrence of solicited treatment-related adverse events at 56 days. In a planned pharmacokinetic (PK) sub-study we aim to assess PK/pharmacodynamic (PD) of oral vs IV rifampicin, describe LZD and RIF PK and cerebrospinal fluid concentrations, explore PK/PD relationships, and investigate drug-drug interactions between LZD and RIF. Safety and pharmacokinetic data from this study will inform a planned phase III study of intensified therapy in TBM.

**
Clinicaltrials.gov registration: **NCT03927313 (25/04/2019)

## Introduction

In Africa HIV-1 associated tuberculous meningitis (TBM) has a 2-month mortality approaching 50%
^
1
^. Although early antiretroviral therapy (ART) is of proven benefit in other forms of tuberculosis (TB)
^
2
^ this has not been demonstrated for TBM
^
3
^, a finding potentially contributed to by exacerbated immunopathology in the confined space of the central nervous system (CNS)
^
4
^. Furthermore only a few clinical trials have addressed the recognized poor penetration of several antitubercular agents into cerebrospinal fluid (CSF) and adjunctive corticosteroids have not shown unequivocal benefit for HIV-1 co-infected patients in clinical trials
^
5
^. The recommended management of patients with TBM has remained unchanged for decades. The need to develop an effective drug treatment regimen combining agents to ensure effective bacterial killing, as well as therapies to control the host immune response is urgent.

### Linezolid

Linezolid (LZD) is currently used as an effective rescue therapy in extensively drug resistant TB
^
6–
11
^. Its use is also established for the treatment of gram positive infections including pyogenic brain abscesses where patients receive 1200mg for four weeks
^
12
^. LZD is an attractive agent for the treatment of TBM due to its potent efficacy against
*Mycobacterium tuberculosis (M.tb)* as well as its excellent CNS penetration
^
12
^. Two published studies have investigated its potential role in TBM; the first, an observational study demonstrated favorable clinical outcomes and a non-significant difference in adverse events in children with drug sensitive TBM treated with LZD compared to control
^
13
^; the second, a retrospective cohort study of 33 adults with TBM found that the addition of LZD to a standard regimen led to more rapid improvement in CSF parameters, recovery of consciousness and reduction of fever
^
14
^.

LZD toxicity has however limited its use. The most common adverse events (AE) associated with LZD use in TB treatment are haematological toxicity (mainly dose-related) and peripheral neuropathy (mainly duration-dependent)
^
15
^. These are usually mild and are reversible with dose reduction or treatment interruption if identified early. In a systematic review, AE related to LZD use at doses > 600 mg/day occurred at a median of 252 days (IQR 120 – 540) of LZD exposure
^
16
^. In the
*NiX-TB* trial
^
17
^ where LZD was given at a total dose of 1200mg per day for 6 months, peripheral neuropathy occurred in 81% of cases with the majority of these occurring after 3 months of treatment. Median time to return to a normal or mild neuropathy score was 3 months. Myelosuppression was the second most common AE occurring in 48% of cases. Although these AE led to frequent treatment interruption (66% of cases had treatment interruption) all 109 participants completed 26 weeks of treatment. In the context of TBM, where morbidity and mortality are high, the risk-benefit of this potent antituberculous agent with good CNS penetration requires further evaluation in the context of a phase II safety trial.

### Aspirin

Aspirin (ASA) is a safe, widely available and inexpensive drug with effects on the pathogenic processes recognised as integral to the pathogenesis of TBM and its complications
^
18,
19
^. In a placebo-controlled trial of ASA in 118 adult patients with TBM in India, 150mg daily ASA was associated with a significantly lower 3-month mortality and a lower incidence of stroke albeit not significant
^
20
^. Following this a similar study in South Africa randomized 146 children with TBM to receive low dose (75mg/24hours) (n=47) or high dose (1000mg/24 hours). In this trial there was no significant effect of ASA on mortality however there was a significant reduction on incidence of new hemiplegia in those receiving high dose ASA
^
21
^. In a recent study in Vietnam, HIV-1 uninfected individuals with TBM received ASA in addition to standard care. Patients were randomised to receive either placebo, ASA 81mg OD or ASA 1000mg OD for 56 days. The pre-specified sub-analysis of results demonstrated a potential reduction in new infarcts and deaths by day 60 in patients with microbiologically confirmed TBM receiving 1000mg OD of ASA
^
22
^. Its safety for use in HIV-1 infected individuals with TBM, particularly when used in combination with an intensified antituberculous regimen, has yet to be investigated. 

### High dose rifampicin

Rifampicin (RIF), one of the four first line treatments for TBM demonstrates poor penetration of the blood brain barrier (BBB) with total concentrations in CSF only 10–20% of that reached in plasma
^
23
^.
*In vitro*, animal and early bactericidal activity studies suggest that the standard 600mg once daily dose is at the lower end of the dose response curve
^
24
^. This has prompted a series of studies in both pulmonary and extrapulmonary tuberculosis investigating the safety and efficacy treatment regimens containing higher doses of RIF
^
25–
32
^. None of these studies have detected a significant safety signal thereby supporting the safety of RIF up to doses of 35mg/kg. Similarly, they provide evidence to suggest superior efficacy when used at a dose of 35 mg/kg compared to 20 mg/kg
^
28,
29,
31,
32
^.

In TBM, the use of higher RIF doses is appealing given its incomplete penetration into the central nervous system. In 2013 an open-labelled randomized phase 2 study in 60 Indonesian adults with TBM showed a 50% reduction in mortality with higher dose intravenous RIF (13 mg/kg, which equates to an approximate oral dose of 20mg/kg) compared with standard dose oral therapy
^
33
^. This intensified treatment did not result in increased toxicity and was associated with a substantially lower 6-month mortality. A subsequent large randomised placebo-controlled trial in Vietnam evaluated a combined regimen of oral RIF 15 mg/kg plus levofloxacin. Unlike the previous trial using intravenous therapy (at higher equivalent oral doses of 20 mg/kg) there was no effect of mortality
^
25
^. These results, plus evidence from pre-clinical studies and pulmonary TB, provide adequate justification to systematically assess the effect on outcomes in TBM with RIF doses > 20 mg/kg.

The proposed trial combines three drugs for which there is sufficient evidence to suggest adequate safety profiles and potential benefit in a condition in which there is high mortality and inadequate treatment. Their safety in combination and in the context of HIV-1 co-infection requires careful evaluation in a controlled Phase II trial before this regimen can be tested in the context of a phase III clinical trial.

Our primary hypothesis is that increased dose RIF plus LZD and ASA can be safely added to standard therapy for HIV-1-associated TBM.

## Methods

This protocol is reported in line with the Standard Protocol Items: Recommendations for Interventional Trials (SPIRIT) guidelines
^
34
^.

The primary aim of this study is to investigate the safety of enhanced antimicrobial therapy including increased dose RIF and LZD with or without adjunctive ASA added to standard therapy for TBM in HIV-1 infected adults.

The secondary aims are:

a.To determine CSF
*M.tb* culture positivity and Gene Xpert® Ultra positivity at baseline and at 3 and 28 days post treatment by allocation.b.To evaluate the effect of ASA and enhanced TB treatment on the incidence of immune reconstitution inflammatory syndrome (IRIS) in participants starting ARTc.To evaluate the effect of high dose RIF and LZD with and without ASA on CNS imaging (CT, MRI and MR Spectroscopy) in conjunction with clinical, immunological and transcriptional profiling.d.To determine i) whether host genotype, including leukotriene A4 hydrolase (LTA4H) genotype, influences therapeutic effect of ASA in HIV-TBM and ii) the pharmacogenetic influence on RIF and LZD exposures and toxicity.

Three sub studies will recruit all consenting participants with the following aims:

### Sub study 1 (
*Pharmacokinetic-pharmacodynamic*)

1. To describe the plasma and CSF PK of LZD and high dose RIF.

2. To evaluate the relationship between drug exposures, toxicity and efficacy.

3. To compare exposures between intravenous and oral RIF administration.

4. To investigate the impact of high dose RIF on LZD availability.

### Sub study 2 (
*Pathogenesis*)

1. To evaluate the effect of high dose RIF and LZD, with and without ASA on the transcriptional signature derived from whole blood and CSF RNA sequencing, as well as the metabolomic and proteomic profiles, in TBM.

### Sub study 3 (
*Neurocognitive and functional outcomes*)

1. To describe the frequency and characteristics of neurocognitive impairment following HIV-associated TBM

2. To compare neurocognitive outcomes with: i) presence and location of structural abnormalities on magnetic resonance imaging, ii) radiological makers of metabolic dysfunction on magnetic resonance spectroscopy, iii)
*in vivo* markers of neurodegeneration and brain injury within the central nervous system

3. To quantify the functional impairment (including effect on quality of life) of TBM associated neurocognitive impairment

A strategic aim of LASER-TBM is to serve as a planning study to generate data which will inform a planned phase 3 RCT of intensified treatment in TBM (INTENSE-TBM). Data from LASER in particular i) pharmacokinetic data on exposure in intravenous versus high oral dose rifampicin and ii) safety data to exclude any signal which would preclude commencement of INTENSE-TBM will in part dictate the resulting sample size. If no safety signal is detected, and PK endpoints met with adequate power then LASER-TBM recruitment may cease prior to the maximum sample size of 100 participants to allow timely commencement of INTENSE-TBM.

## Study design, recruitment and duration

LASER-TBM is a parallel group, randomised, multi-arm Phase 2A trial evaluating the safety of increased dose RIF plus LZD, with or without ASA, for the treatment of HIV-infected adults with TBM (
Figure 1). HIV-1 infected adults with newly-diagnosed TBM (up to n = 100) will be recruited from five public-sector hospitals across South Africa. Participants will be randomised in a 1.4:1:1 ratio across two experimental (n = 30 each) and one standard of care (n = 40) arms (
Figure 1). Relatively more participants will be randomised to the control group to account for the higher mortality anticipated in the standard of care arm. 

**Figure 1. f1:**
[figure not shown]
Study design schematic describing randomisation to study arms, treatment intervention per am, visit schedule, overview of clinical procedures and timepoints relating to primary and secondary endpoint data collection. RHZE: Rifampicin, Isoniazid, Pyrazinamide, Ethambutol; R
_10_: Rifampicin 10mg/kg/day; R
_35_: Rifampicin 35mg/kg/day; LZD: Linezolid; ASA; Aspirin.

Treatment will be provided in all arms for 56 days, after which participants will be referred back to public sector facilities to complete standard therapy for HIV-associated TBM. All participants will receive antitubercular chemotherapy as well as corticosteroids as per standard practice. Participants allocated to experimental arms 2 and 3 will receive additional RIF (total oral dose 35 mg/kg/day once daily) for 56 days plus oral LZD 1200mg once daily for the first 28 days, reduced to 600 mg daily for the next 28 days. Those randomised to experimental arm 3 will also receive oral aspirin 1000 mg once daily for 56 days. A second randomization will take place before receipt of study drug for participants in the experimental arms (n = 60) to receive either oral (35 mg/kg) or intravenous (20 mg/kg) RIF (see
Figure 2). This will be continued for 3 days, after which all participants will receive oral RIF for the remainder of the intervention period (53 days). 

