**Figure 3. f3:**
[figure not shown]
Schematic to summarise intensive pharmacokinetic (PK) sampling schedule. All participants (n=100) will be offered participation in the intensive sampling component of the PK sub-study at the time of randomization to the main study. Intensive plasma sampling will take place at the Day 3 study visit. Serial venous blood samples will be collected through a peripheral intravenous catheter pre-dose, and at 0.5, 1, 2, 3, 6, 8 - 10, and 24 hours after witnessed drug intake and an overnight fast. Sparse sampling will be performed at Day 3 for participants who decline intensive sampling or in whom this fails.

**The primary endpoint of the study is:** The incidence of solicited treatment-related AE (see
Table 1) and death at 56 days associated with increased dose RIF plus LZD with or without adjunctive ASA, when administered alongside standard antitubercular therapy.

**Table 1. T1:** Solicited treatment related adverse events, objective measures for assessment and management plan in each setting. Grade relates to Division of AIDS (DAIDS) criteria
^
37
^. ASA, Asprin; RIF, Rifampicin; LZD, Linezolid.

Adverse Event (responsible study drug)	Objective measure	Parameter	Management
Gastrointestinal haemorrhage (ASA)	Clinical and laboratory measures suggesting GI haemorrhage.	i) Vomiting fresh or changed blood of any volume, ii) Melena, iii) Unexplained drop in Hb concentration of >2g/L or iv) > 5mls of fresh or changed blood aspirated from nasogastric tube.	Discontinue study drug permanently.
Intracerebral haemorrhage (ASA)	Radiological evidence of haemorrhage.	CT or MRI finding	Discontinue study drug permanently.
Transaminitis (RIF)	alanine tranferase (ALT), bilirubin	New Grade 3 or above	Discontinue study drug (and other potentially hepatotoxic agents). Place on alternative treatment for TBM if background regimen affected. Re-test every 2 days. Resume study drug with an escalating dose rechallenge once ALT < 100 IU and total bilirubin within normal range.
Anaemia (LZD)	Hemoglobin (Hb)	New Grade 3	Discontinue study drug (plus any other myelosuppressive drugs as appropriate). Consider transfusion with packed cells or erythropoietin therapy. Monitor Hb twice weekly. Restart at 50% dose once Hb ≥ 8 mg/dL
		New Grade 4	Discontinue study drug permanently. Consider hospital admission and/or transfusion with packed cells or erythropoietin therapy. Re-test every 2 days.

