## Interventions

### Study drug regimens

Participants enrolled to the study will receive study drug regimens as outlined in
Table 2. Dosing of the RHZE fixed dose combination (FDC) will be according to World Health Organisation (WHO) weight bands
^
38
^. Study drugs will be given orally, either as tablets/capsules or crushed, depending on the clinical circumstances. Half of participants in experimental arms will be randomised to receive IV RIF for the first 3 days of therapy and switched to the oral formulation thereafter. Study drugs will be prescribed by trial doctors, packaged and distributed by trial pharmacists.

**Table 2. T2:** Details and dosing of study drug regimen - provided for 56 days post randomisation.

	Drug					
Arm	RIF	INH	EMB	PZA	LZD	ASA
**1**	10 mg/kg O.D.	5 mg/kg O.D.	15 mg/kg O.D.	25 mg/kg O.D.		
**2**	35 mg/kg O.D.	5 mg/kg O.D.	15 mg/kg O.D.	25 mg/kg O.D.	1200 mg O.D. (28 days) then 600 mg O.D. (28 days)	
**3**	35 mg/kg O.D.	5 mg/kg O.D.	15 mg/kg O.D.	25 mg/kg O.D.	1200 mg O.D. (28 days) then 600 mg O.D. (28 days)	1000 mg O.D.

O.D.: Once daily.

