### Intravenous RIF

Participants allocated to experimental arms will be randomised (1:1) to receive either oral RIF 35 mg/kg or IV RIF 20 mg/kg once daily for the first 3 days of therapy (in addition to HZE and LZD with or without ASA, according to the experimental arm). Those randomised to IV RIF will receive the full RIF dose intravenously, plus additional antitubercular drugs as individual ablets (at standard doses). IV RIF will be administered as an infusion as per the package insert and according to a detailed SOP. These are described in
Table 3B.

**Table 3B. T3b:** Weight bands for intravenous rifampicin (RIF) dosing.

	Band 1	Band 2	Band 3	Band 4	Band 5	Band 6
Weight range	30 – 33 kg	34 – 37 kg	38 – 54 kg	55– 65 kg	66 – 70 kg	> 70 kg
HZE tabs	2	2	3	4	4	5
R _20_ IV	900	1050	1200	1350	1500	1650
Total RIF	900	1050	1200	1350	1500	1650

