**Blood**								
Weight		x	x	x	x	x	x	
Haematology: FBC and white cell differential								
Biochemistry: Creatinine, eGFR, electrolytes, LFTs	x		x	x	x	x	x	
INR	x		x			x		
HIV-1 ELISA +/- HIV Rapid Test (x2) if required	x							
CD4+ count, HIV Viral Load		x						
Plasma for PK sub-study (sparse sampling)						x	x	
Plasma for PK sub-study (intensive sampling – if consented)			x					
Stored plasma for immunological, proteomic and metabolomic profiling		x	x	x	x	x	x	
PBMC for storage		x	x			x		
Whole blood for RNA extraction		x	x	x	x	x	X	
Whole blood for DNA extraction (if consented)		x						

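### The Day 3 (±1 day) visit window lets PK samples fall on Day 4, after the 3-day randomised IV rifampicin period has ended, and Day 3 is the only visit that can compare routes

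*Protocol article*

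**What the plan says.** **Duration of the randomised route.** Three places in the protocol article agree. The study design text after Figure 1 says "This will be continued for 3 days, after which all participants will receive oral RIF for the remainder of the intervention period (53 days"), within a total set by "Treatment will be provided in all arms for 56 days". The section on intravenous RIF gives "IV RIF 20 mg/kg once daily for the first 3 days of therapy". The section on study drug regimens says "Half of participants in experimental arms will be randomised to receive IV RIF for the first 3 days of therapy and switched to the oral" (that is, to oral drug from then on).

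**Timing of PK sampling.** The Figure 3 legend says "Intensive plasma sampling will take place at the Day 3 study visit". The fallback has the same anchor: "Sparse sampling will be performed at Day 3 for participants who decline intensive sampling or in whom this fails". In Table 4 the row "Plasma for PK sub-study (intensive sampling – if consented") is marked only in the Day 3 column, and that column carries a window of plus or minus 1 day. The CSF PK row is marked at Days 3 and 28. The scheduled sparse plasma samples are at Days 28 and 56.

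**Use of the comparison.** Sub study 1 lists comparing exposure between IV and oral rifampicin as an aim. The Figure 2 legend describes the outcome of the second randomisation as a PK endpoint. The strategic aim, stated at the end of the sub-study descriptions, names "pharmacokinetic data on exposure in intravenous versus high oral dose rifampicin" among the data that will partly set the final sample size. It also allows recruitment to stop before 100 if, among other things, PK endpoints are met.

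**The concern.** The second randomisation creates a difference between groups that lasts three once-daily doses. The sampling visit meant to measure that difference has a window that runs past it. No later visit can recover the comparison, because at Days 28 and 56 everyone is on oral drug.

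A late sample from an IV-allocated participant does harm in one of two ways:

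- Analysed as randomised, it adds an oral profile to the IV group and pulls the ratio towards 1, from whichever side the truth lies.
- Excluded, or analysed by the route actually received, it reduces the number of randomised IV profiles. It also weakens the protection of randomisation if late sampling is related to how ill the participant is.

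At stake is a stated PK aim that feeds the decision to close recruitment early. A pull towards 1 matters most if the question is whether the two routes give similar exposure. The primary safety endpoint is not affected.

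**Working it through.** **1. The article's own figure.** 56 days in total − 3 days of randomised route = 53 days of oral drug for all. This reproduces.

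**2. Window against dosing days.** Inputs: three once-daily IV doses (study design text, intravenous RIF section) and permitted visit days 2, 3 and 4 (Table 4). The article does not say whether the first dose is on Day 0 or Day 1.

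| First dose counted as | IV doses on | Day 2 sample | Day 3 sample | Day 4 sample |
|---|---|---|---|---|
| Day 1 | Days 1–3 | IV | IV | oral |
| Day 0 | Days 0–2 | IV | oral | oral |

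Under either count, at least one permitted day lies after the IV course.

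**3. Dilution if analysed as randomised.** Let f be the share of IV-allocated profiles taken on an oral dose. On the log scale a share 1 − f of the contrast is kept, so the apparent ratio = (true ratio)^(1 − f). Neither f nor the true ratio is in the article, so both are assumed below.

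*A plausible true ratio.* The Introduction equates 13 mg/kg IV with about 20 mg/kg oral. Scaling proportionally (an assumption, since rifampicin kinetics may not be linear):

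- 20 mg/kg IV ≈ 20 × 20/13 = 30.8 mg/kg oral
- against 35 mg/kg oral: 30.8/35 = 0.88

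| f (assumed) | Apparent ratio when the true ratio is 0.88 |
|---|---|
| 10% | 0.88^0.90 = 0.89 |
| 20% | 0.88^0.80 = 0.90 |
| 33% | 0.88^0.67 = 0.92 |

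The shift is 0.01 to 0.04.

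*Sensitivity of that ratio.* The same scaling applied to the banded doses in Tables 3A and 3B gives, for example, 900 × (20/13)/1500 = 0.92 at 30–33 kg, 1050 × (20/13)/1500 = 1.08 at 34–37 kg and 1650 × (20/13)/2700 = 0.94 above 70 kg. The other bands lie between 0.99 and 1.03. The closer the true ratio is to 1, the less there is to dilute.

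**4. Loss if late profiles are excluded.** Input: n = 60 randomised 1:1 (Figure 2 legend), so at most 30 per route. The standard error of the log ratio, relative to 30 against 30 and with equal variances assumed, is √[(1/(30(1 − f)) + 1/30)/(2/30)].

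| f (assumed) | IV profiles left | Relative standard error |
|---|---|---|
| 10% | 27 | √1.056 = 1.03 |
| 20% | 24 | √1.125 = 1.06 |
| 33% | 20 | √1.25 = 1.12 |

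**The case against.** The strongest reply is that the two rules were meant to align. IV drug is given for the first three days of therapy and sampling is on Day 3, so the natural reading is that the profile belongs to the third IV dose. The ±1 day is a general visit window that also covers examination, bloods and lumbar puncture, while the dedicated PK text says Day 3 without tolerance. Trial procedures take place in hospital during the admission, so an on-time profile is practicable. Route is unblinded and drug intake is witnessed for the sampled dose, so staff would know which route was measured. The aim is worded in terms of administration, which may mean route received, and then no dilution arises. The PK analysis belongs to an analysis plan that is not shown, IV administration follows an SOP, and the schematics in Figures 1 to 3 are not visible here.

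Much of this limits the consequence. Dilution does require that an oral profile be counted as IV, and the absence of a route check from the article is not in itself an error. It does not remove the conflict: the article prints one window for the Day 3 column, puts the PK rows in that column, and gives no narrower limit for them. If late profiles are handled by route received, the cost becomes lost randomised IV profiles rather than bias.

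A reader might also infer more than the text supports:

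- *That no IV/oral contrast remains at all.* This needs the first dose to be Day 0 and every sample to be on Day 3 or later. The article nowhere numbers enrolment as Day 0. Counting treatment from randomisation leaves the point open, which is a reason to define Day 1 and nothing more.
- *That a large ratio is being heavily diluted*, for example a true 1.5 reading as 1.31. No such ratio appears in the article, and its own equivalence figure points to a value near or slightly below 1.
- *That this comparison decides whether phase 3 goes ahead.* The strategic aim gives it a part in setting the sample size and in early closure. It is the safety data that could preclude the next trial.

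**Conclusion.** The conflict is real. As printed, the sampling window extends at least one day beyond the randomised IV period whichever way days are numbered, and no other PK visit can compare the routes.

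Its size cannot be determined from the article. With an assumed ratio of 0.88 and 10% to 33% late samples, the bias is 0.01 to 0.04 on the ratio. If late profiles are dropped instead, 3 to 10 of 30 IV profiles are lost and the standard error rises by 3% to 12%. These figures rest on proportional scaling of one stated equivalence, on assumed late shares, and on all 60 participants contributing a profile. They illustrate the effect and do not predict it. The point concerns a PK aim with a role in early closure, and correcting it is cheap.

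**What to change.** Leave treatment as it is and reconcile the sampling window with the randomised period:

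1. State which calendar day is Day 1 relative to the first rifampicin dose.
2. Require every Day 3 PK sample in the experimental arms (intensive plasma, sparse plasma and CSF) to relate to a dose given while the randomised route is still in use, with no plus-day tolerance for PK. The general ±1 day window can stay for the other Day 3 assessments. The 24-hour sample of the intensive profile belongs to the same dose, so it should precede the next one.
3. Record the route of the sampled dose on the case report form, and check it against allocation before the IV/oral ratio is estimated. With 52 participants already enrolled, apply the same check to profiles already taken and report how many were late.

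The cost is a change of wording in the visit schedule, one case report form field, and less flexible timing for PK sampling.
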